#### Outcomes at 24 hours

2.5.3

Patients will be contacted by telephone the next day, 24 hours after surgery, to ask the following questions:

(1)What was your average pain score over the last 24 hours after discharge, on a scale of 0 to 10 (NRS)?(2)Rebound pain: Is the nerve block still providing pain relief? Yes or NoAt what time following the surgery did the block wear off?At what time following the surgery did you take your first dose of opioid?(3)Are you continuing to use opioids postoperatively? If yes, provide drug name, frequency, and amount over the past 24 hours.(4)Are you satisfied with your postoperative pain control (Likert scale 1–7)?

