#### Inclusion criteria

2.2.1

Patients aged >18 years undergoing elective arthroscopic shoulder joint repairs admitted for a day surgical procedure, with the ability to provide informed consent.

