#### Exclusion criteria

2.2.2

Not consenting; contraindications to spinal injections as per the American Society of Regional Anesthesia and Pain guidelines^[25]^; known allergy to LA; allergy to all opioid medications; diagnostic shoulder arthroscopic procedures; inability to understand or comprehend in English language; history of daily opioid medication use for the past 1 month; and patients with planned overnight hospital stay.

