#### Secondary outcomes and measurement

2.5.2

The following secondary outcomes will be collected during the in-hospital stay and follow-up of study patients:

(1)Total opioid consumption in hospital (until discharge): opioid use will be converted into morphine equivalent dosage for analysis.(2)Pain intensity: pain scores with movement in PACU; pain scores at rest; and movement at readiness to discharge. Since patients will be asked not to move their shoulders by the surgical team, pain scores with movement will be collected by asking the patient to sit up from lying down position. Pain scores will be collected using the 11-point NRS scale.^[26]^ We will record the postoperative time of peak pain scores.(3)Safety outcomes: incidence of moderate to severe PONV and incidence of moderate to severe itching will be collected using validated scales^28^,^29^; incidence of ipsilateral diaphragmatic paralysis will be diagnosed using bedside US examination with sniff test,^[30]^ 30 minutes after admission. This has been observed to be valid and clinically feasible^[31]^; and incidence of respiratory depression^[32]^ and LA toxicity^[33]^ will be diagnosed based on clinical symptoms and signs. All these outcomes will be noted postoperatively in PACU and until discharge, unless specified.(4)Sensory blockade on the side of the operated shoulder: Sensory assessment of shoulder area will be performed by a trained research assistant. Sensory dermatomes corresponding to shoulder and upper arm and their blockade to cold sensation will be noted. In total we will observe sensory blockade in 7 dermatomal areas (Supplemental Digital Content (Appendix 1)) and compare the extent of blockade between the 2 groups by their median and range.^[34]^
(5)Patient satisfaction with postoperative analgesia: This will be recorded at hospital discharge and 24 hours and at 1 month after surgery (by a telephone call) and measured using a 7-item Likert scale.

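### The 24-hour telephone script sets a pain recall window that cannot exist, and its rebound-pain item collects no pain score

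*Protocol article*

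**What the plan says.** Section 2.5.3 fixes the time of the call: "Patients will be contacted by telephone the next day, 24 hours after surgery, to ask the following questions". Its first question is "What was your average pain score over the last 24 hours after discharge, on a scale of 0 to 10 (NRS".

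The second item begins "Rebound pain: Is the nerve block still providing pain relief". It goes on to ask when the block wore off, and then "At what time following the surgery did you take your first dose of opioid". The third item asks whether opioids are still being used: "If yes, provide drug name, frequency, and amount over the past 24 hours".

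Three other places bear on this:

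- Sections 2.2.1 and 2.2.2 restrict the trial to patients "admitted for a day surgical procedure" and exclude "patients with planned overnight hospital stay".
- Section 2.4.4 has nurses giving intravenous opioids in the PACU in both groups, followed by a stay in the day surgery unit before discharge.
- Section 2.5.2 has a separate outcome, "Total opioid consumption in hospital (until discharge"), and also collects NRS scores at rest and with movement when the patient is ready to leave.

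Section 1.2 dates the 24-hour pain and opioid outcomes from the operation, not from discharge.

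**The concern.** The pain question counts from discharge, while the call is timed from surgery. Because every patient spends some time in the PACU and the day surgery unit, the period named in the question has not elapsed when it is asked. Each patient has to choose a period, and the analyst cannot tell which one was chosen.

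The rebound item has a different fault. Rebound pain is a rise in pain once a block wears off. The questions under that heading give a yes/no answer and two times. Neither a duration of block nor a time to first opioid says whether pain rose, or by how much.

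At stake are the interpretation of the 24-hour average pain score and any statement about rebound pain, which the Introduction names as a drawback of the interscalene block when arguing for an alternative. A pain score that was not asked for at the call cannot be recovered later.

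**Working it through.** The plan states no figure that depends on these items. Its sample size (section 2.6.1) concerns the resting score 30 minutes after PACU admission and does not enter here.

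**1. The pain window.** Inputs: call at 24 h after surgery (2.5.3); discharge at *h* hours after surgery, with *h* > 0 because patients pass through PACU and day surgery unit (2.4.4). The article gives no value for *h*, so I assume 2 to 8 h.

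Time at home when the call is made = 24 − *h*. Share of the 24 h since surgery spent in hospital = *h*/24.

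| *h* (assumed) | Hours at home at the call | Hospital share of 24 h |
|---|---|---|
| 2 | 22 | 8.3% |
| 3 | 21 | 12.5% |
| 4 | 20 | 16.7% |
| 6 | 18 | 25.0% |
| 8 | 16 | 33.3% |

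The contradiction does not depend on the assumed range: for any *h* above zero, 24 − *h* is below 24.

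**2. How far the two readings can differ.** Take a time-weighted average, with mean pain *a* in hospital and *b* at home. Averaging since surgery gives [*h·a* + (24 − *h*)·*b*]/24; averaging since discharge gives *b*. The difference is (*h*/24)(*a* − *b*). For each point by which hospital and home pain differ, the readings differ by 0.08 points (*h* = 2) to 0.33 points (*h* = 8). For a gap of 2 points, which section 2.6.1 treats as clinically meaningful between groups, that becomes 0.17 to 0.67. This is a shift in an individual answer, not a difference between arms.

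**3. The rebound item.** Question by question:

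- Is the block still working: yes or no, no intensity.
- When did it wear off: a time, no intensity.
- When was the first opioid taken: a time, no intensity.

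Elsewhere, the average score in the first question is one number for the whole period. A patient with steady moderate pain and a patient with little pain followed by severe pain can report the same average. The score at discharge gives a starting level but nothing after wear-off. Section 2.5.2 also records when pain peaked, but that is a time and not a score, and the 24-hour script contains no question on peak pain.

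**4. The opioid item.** Asked 24 h after surgery, the past 24 hours is simply 0 to 24 h, which agrees with section 1.2. What is left open is whether nurse-given doses belong in the answer. They fall inside the window and are already in the in-hospital total of section 2.5.2. The first-opioid question has the same gap, since the first opioid after surgery may be one given in the PACU.

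**The case against.** The strongest reply is that this is a slip of wording in secondary telephone items. Patients will answer for roughly the time at home, and the question is the same in both arms under a double-dummy, blinded design (2.3.3), so the effect is noise. That stands.

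On opioids, a reader might infer that hospital doses are counted twice and the 24-hour outcome is contaminated. The article does not support this. The window is coherent, the article never adds the two outcomes together, and a question about continuing use, drug name and frequency reads most naturally as self-taken medication. The hospital shares in the table are shares of hours under an assumed stay. They are not shares of dose and not an error in any outcome.

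On rebound, it can be said that the term is absent from the objectives in section 1.2, that there is no interscalene arm to compare with, and that Table 2 or the full protocol may define the outcome. The first two points limit its importance. The third does not rescue the questions as set out: a definition cannot supply a score that they do not collect.

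A reader might also object that the question about the nerve block is invalid in controls, whose ESP injection is saline. Every patient receives both injections and is blinded, so identical wording is proper, and controls may well report when their relief faded. This is a minor point of phrasing.

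**Conclusion.** The point holds in two parts. The recall window of the 24-hour pain question cannot exist for a day-surgery patient, whatever the length of stay. The rebound-pain item measures block duration and time to first opioid, not rebound pain. A third, smaller part is that the opioid question does not say whether hospital doses are to be included.

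The consequence is added noise and ambiguity in the 24-hour pain score and no usable value for rebound pain. With an assumed stay of 2 to 8 hours, the two readings of the pain question differ by 0.08 to 0.33 points for each point of difference between hospital and home pain. No directional bias between arms is shown or claimed. Only secondary outcomes are touched. It is worth correcting because the remedy is cheap and the missing score cannot be obtained afterwards.

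**What to change.** - **Average pain:** use one window, for example *since you left hospital*, and make sure the discharge time is recorded. A 0 to 24 h window would also serve and would match section 1.2; what matters is that only one is used.
- **Opioids:** ask for opioids taken at home since discharge. If a 0 to 24 h total is wanted, add the charted in-hospital dose to it. State whether the first opioid means the first after discharge.
- **Rebound:** add one question, *worst pain since leaving hospital (0–10), and at what time*, to be read against the discharge NRS already collected. Otherwise rename the item block duration and time to first opioid, and make no claim about rebound.
- **Optional:** replace the reference to the nerve block with wording that covers both injections.

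The cost is a reworded script and about one extra minute per call. The primary outcome, the sample size and the other procedures stay as they are.

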### Objectives

1.2

The primary objective of this study is to determine whether ESP block is superior to PAI for in-hospital postoperative analgesia among patients who have undergone arthroscopic shoulder surgical repair. This will be determined by comparing the resting pain scores after initial stabilization in the postanesthetic care unit (PACU).

Secondary objectives will be to compare:

(1)resting pain scores at discharge;(2)pain scores with movement in PACU and at discharge;(3)total opioid consumption in hospital;(4)incidences of postoperative nausea and vomiting (PONV), itching, ipsilateral diaphragmatic paralysis, respiratory depression, and LA toxicity in hospital;(5)sensory blockade assessment in PACU;(6)patient satisfaction at discharge,(7)average pain scores, persistent surgical site pain and opioid use at 24 hours and at 1 month postoperatively.

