#### Achievement of blinding

2.3.3

Since the medication syringes contain clear solutions, and the study uses a double dummy technique for blinding by performing both interventions in each patient, patients, physicians, other healthcare providers, and data collectors are effectively blinded. Apart from the statistician who has prepared the randomization code and the pharmacist preparing the study medications, all other personnel are blinded for assessment and data analysis.

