##### Saline ESP block, active PAI

2.4.2.1

The ESP block will be performed similar to above, but with 30 mL of saline injected as 5 mL aliquots, immediately before surgery. The orthopedic surgeon will perform an active PAI at the end of surgical procedure, on the operated side rotator cuff using 30 mL of 0.25% bupivacaine with 5 μg/mL of epinephrine injected in 5 mL aliquots. The procedure will be performed as described above.

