#### Statistical analysis

2.6.2

The trial will be reported as per the consolidated standards of reporting trials standards for reporting randomized trials.^[38]^ The study will be analyzed using an intention-to-treat (ITT) approach. For ITT, we will analyze patients within their randomized groups. We will use multiple imputation strategy to account for missing outcomes in ITT. Normally distributed continuous data will be reported as means and standard deviations; skewed continuous data will be reported as medians and quartiles (Q1 and Q3); and nominal data, categorical or binary data will be reported as counts and percentages. Comparison of normal continuous outcomes will be performed using Student *t* test for unpaired groups. Comparison of non-normal or skewed continuous outcomes will be performed using Mann–Whitney *U* test. Categorical outcomes will be compared using Pearson Chi-squared test. Each test will be 2-sided with a significance level of 0.05. Up-to-date versions of SAS (Cary, NC) and SPSS (Chicago, IL) will be used to conduct all analyses. Dichotomous outcomes will be reported as relative risk and relative risk reductions and continuous outcomes as difference in means with standard deviations. Precision will be reported using 95% confidence intervals. No subgroup tests will be conducted. Individual outcomes and their analyses are summarized in Table 2.

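### The 24-hour wear-off question names the nerve block, which is saline in the control arm, so it may not measure the same thing in both arms

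*Protocol article*

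**What the plan says.** Section 2.5.3 (Outcomes at 24 hours) sets a single next-day contact: "Patients will be contacted by telephone the next day, 24 hours after surgery, to ask the following questions". Under the label of rebound pain it asks "Is the nerve block still providing pain relief", to be answered yes or no, then when after surgery the block wore off, then when the first opioid was taken. The 1-month questions (2.5.4) do not return to wear-off.

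Section 2.3.3 explains that "the study uses a double dummy technique for blinding by performing both interventions in each patient". For the control arm, section 2.4.2.1 states "The ESP block will be performed similar to above, but with 30 mL of saline injected as 5 mL aliquots, immediately before surgery", and then "The orthopedic surgeon will perform an active PAI at the end of surgical procedure", with bupivacaine.

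Section 2.6.2 assigns continuous outcomes to the t test or the Mann–Whitney test and adds "We will use multiple imputation strategy to account for missing outcomes in ITT". It refers to Table 2 for individual outcomes; that table is not shown.

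The secondary objectives for follow-up (1.2) are "average pain scores, persistent surgical site pain and opioid use at 24 hours and at 1 month postoperatively". Block duration is not among them, nor in the secondary outcome list in 2.5.2.

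**The concern.** The wording ties the item to one of the two injections. In the ESP arm that is the injection with the drug. In the control arm it is the saline one, and the drug was given by a route that the Introduction lists separately from regional blocks. A control patient who takes the words literally may say that the block never worked, or give no time, while the infiltration is still acting. Another control patient may answer for whatever relief is felt. The two answers measure different things, and nothing in the printed questions separates them. Because this is a fault of data collection, no analysis can later recover what the patient meant.

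A second, smaller matter concerns the time itself. A patient who says the block is still working at the call has no wear-off time, and no later contact supplies one. That value is right-censored. If it were handled as an ordinary missing value, the patients with the longest relief would be dropped or given unsuitable imputed times.

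At stake is the reading of rebound pain. The Introduction names rebound pain as one of the risks of the interscalene block that motivate the study of ESP.

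**Working it through.** **1. What the question refers to in each arm** (2.3.3, 2.4.1.1, 2.4.2.1, 2.5.3)

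| | ESP arm | Control arm |
|---|---|---|
| Nerve block (ESP, before surgery) | bupivacaine | saline |
| Infiltration (end of surgery) | saline | bupivacaine |
| Literal object of the question | active injection | inert injection |
| Source of any local anesthetic relief | the same injection | the other injection |

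A literal answer is about active drug in one arm and saline in the other. A non-literal answer (any relief felt) refers to active drug in both. The mix of the two kinds of answer in the control arm is unknown, so neither the size nor the direction of the bias can be computed.

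**2. What is known about a patient still blocked at the call**

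The Yes/No item records the answer, and the call is set at 24 hours. A yes therefore means a wear-off time of more than about 24 hours. The information is collected; only the exact time is absent.

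**3. How the general rules fit that answer**

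The t test and the Mann–Whitney test need a value for each patient. If the absent time were treated as missing, an imputation model would learn only from patients whose block had ended by the call. No patient who answers yes has a time, so the data hold nothing from which to model times beyond 24 hours. The absence depends on the duration itself.

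**4. Illustration of the loss if these patients were dropped**

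The plan states no figure for block duration, so there is none to reproduce. All durations below are assumed: lognormal, log-SD s = 0.5, 30 patients per arm (the planned size in 2.6.1), valid answers in both arms, 3,000 simulated trials per row.

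- Share still blocked at 24 h, for median m: 1 − Φ(ln(24/m)/s). For m = 16: ln(1.5)/0.5 = 0.811, giving 21%. For m = 10: ln(2.4)/0.5 = 1.751, giving 4%.
- Median among those under 24 h: m·exp(s·Φ⁻¹(0.5·Φ(ln(24/m)/s))). For m = 16 this is 14.0 h and for m = 10 it is 9.75 h. The difference is 4.3 h instead of 6 h.

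| Assumed medians, ESP vs infiltration (h) | Still blocked at 24 h | Difference in medians: true → after dropping (h) | Shrinkage | Mann–Whitney power: dropped vs ranked at 24 h |
|---|---|---|---|---|
| 12 vs 8 | 8% vs 1% | 4 → 3.5 | 12% | 0.79 vs 0.86 |
| 16 vs 10 | 21% vs 4% | 6 → 4.3 | 28% | 0.77 vs 0.94 |
| 20 vs 10 | 36% vs 4% | 10 → 6.1 | 39% | 0.95 vs 1.00 |
| 20 vs 14 | 36% vs 14% | 6 → 3.0 | 50% | 0.38 vs 0.73 |

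Shrinkage is 1 − (difference after dropping)/(true difference); for example 1 − 4.3/6 = 28%. The table concerns censoring only. It does not measure the wording problem.

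**The case against.** The strongest reply is that patients are blinded and receive both injections, so none can know which was inert. All hear the same words, and many will simply report whether they still have relief. The protocol is itself loose with the term: the sample size section (2.6.1) calls the infiltration a block. This stands in part. It means that a bias against the control arm cannot be asserted. It does not make the item comparable, because the intended reading is left to each patient and the literal reading differs by arm.

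A reader might infer that the longest-acting blocks are lost. The documents do not support this, because the Yes/No item identifies those patients. Nor does section 2.6.2 say that they will be dropped or imputed: a recorded yes is an answer, and Table 2 or an analysis plan may settle its handling. The censoring point is therefore a caution about applying the general rules unchanged.

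A reader might also take duration for the main pharmacological result after discharge. Sections 1.2 and 2.5.2 do not name it, and no visible text plans a comparison of duration between arms.

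**Conclusion.** The wording point holds. Asked as printed, the wear-off item need not measure the same thing in both arms, and later analysis cannot repair it. The direction of any bias is uncertain and its size cannot be derived from the documents. It would be too strong to say that duration cannot be derived in the control arm, because a blinded patient may well report relief from either injection.

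The censoring point holds only as a matter of handling: the stated rules do not suit a time that is absent because it exceeds 24 hours. The shrinkage of about 12% to 50% rests wholly on assumed durations and on dropping these patients, which the plan does not say it will do.

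The weight is small. This is a minor 24-hour item. The primary outcome, the resting pain score 30 minutes after PACU admission, and its sample size are unaffected.

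**What to change.** Replace the two questions in 2.5.3 with one neutral pair, read in the same words to every patient: whether pain relief from the injections given for the shoulder is still present and, if not, how long after surgery it stopped. Add a response for relief that was never felt.

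Record the time of the call. Treat an answer of still present as censored at that time. Compare arms with a log-rank test, or with a rank test in which more than 24 hours is the top rank and never worked is the lowest. State that a still-present answer is not a missing value under 2.6.2. Multiple imputation can remain for patients who were not reached.

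The cost is one changed script item and one line of analysis text, with no extra call and no extra patient. The wording must change before calls are made; the analysis line can be settled at any time before unblinding.

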#### Sample size estimation (Table 1)

2.6.1

Existing literature suggests that single-shot ISNBs with general anesthetic could achieve mean postoperative recovery pain scores of 2 to 3 (on a 0–10 visual analog scale),^[35]^ and patients having general anesthetic with PAI block for shoulder surgery report pain scores of 5 to 6 (on a 0–10 NRS) at PACU.^5^,^36^,^37^ We considered a reduction in mean pain scores by 2 points to be clinically meaningful and important. We believe the ESP block has the potential to provide a good quality of analgesia, nearly similar to ISNB with less chance of phrenic nerve blockade. Based on these assumptions, we considered the following for our sample size analysis. For a 2-sided test, assuming a mean pain score of 5.5 (standard deviation of 2.5) in the control (PAI) group, a sample size of 25 per group will have 80% power to detect a statistically significant difference in mean pain scores of 2 or more using a Student *t* test, with an alpha set at 0.05. We expect minimal loss through attrition as the observations happen in hospital before discharge. However, considering the possibility of changes to surgical plan, we decided to set the sample size at 30 per group (which could give us 85% power). Sample size was estimated using (http://biostat.mc.vanderbilt.edu/wiki/Main/PowerSampleSize#PS:_Power_and_Sample_Size_Calculation), version 3.0.43.

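### The 24-hour call asks for the opioid amount only from patients still taking opioids, so the post-discharge dose of those who took some and stopped is not collected

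*Protocol article*

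**What the plan says.** Section 1.2 (Objectives) lists among the secondary comparisons "average pain scores, persistent surgical site pain and opioid use at 24 hours and at 1 month postoperatively". Section 2.5.3 sets the time of the first call: "Patients will be contacted by telephone the next day, 24 hours after surgery, to ask the following questions".

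Two items of that call concern opioids:

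- Item 2, under rebound pain, asks "At what time following the surgery did you take your first dose of opioid". It does not depend on any other answer about opioids.
- Item 3 asks "Are you continuing to use opioids postoperatively? If yes, provide drug name, frequency, and amount over the past 24 hours". Drug, frequency and amount follow only from a yes.

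Opioid given before discharge is a separate outcome in section 2.5.2: "Total opioid consumption in hospital (until discharge): opioid use will be converted into morphine equivalent dosage for analysis". On missing data, section 2.6.2 says "We will use multiple imputation strategy to account for missing outcomes in ITT". The text gives no rule for scoring a no to item 3. Table 2, which lists outcomes and their analysis, is not shown in the copy at hand. The 1-month call (section 2.5.4) uses almost the same question as item 3.

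**The concern.** Item 3 joins two different quantities. The opening question is about status at the time of the call; the follow-up is about a past window of 24 hours. A patient who took two tablets on the evening of surgery and none since belongs in the past window but not in the current status. The printed question therefore skips the dose of someone whose dose falls inside the period it names.

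At 1 month, current status is a sensible thing to ask. One day after day surgery, some patients may already have finished with opioids, and the amount they took is part of what a 24-hour opioid comparison would want to show. A later analysis plan cannot recover an amount that was never asked for.

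The loss also need not be equal between arms. The active erector spinae plane (ESP) injection is given before surgery and the active periarticular infiltration (PAI) at its end, at different sites, so the timing of opioid need, and of stopping, may differ.

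**Working it through.** No figure stated in the article depends on this question, so there is none to reproduce. The check has two parts.

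**1. What the call records for three patients, taking the wording literally**

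| Patient | Item 2: first dose | Item 3: continuing | Amount recorded |
|---|---|---|---|
| (a) Took opioid at home at 8 h and 14 h, then stopped | a time | no | not asked |
| (b) First opioid at 20 h, still taking it | a time | yes | yes |
| (c) Took none | no time | no | not asked |

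Item 2 separates (a) from (c), so the fact of use is largely recoverable. The amount for (a) is not: item 2 gives no drug, frequency or amount, and the in-hospital total ends at discharge. The gap is the period from discharge to the call.

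**2. How large the effect could be**

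Inputs: n = 30 per group (section 2.6.1). The share of patients who took opioid before the call, u, and the share of those who had stopped, s, are not in the documents. The values below are assumptions.

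Patients with no amount recorded = n × u × s. With u = 0.80:

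- s = 0.10: 30 × 0.80 × 0.10 = 2.4 per arm
- s = 0.30: 30 × 0.80 × 0.30 = 7.2 per arm

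*Effect on dose.* If those patients were entered as zero, the recorded arm mean would be the true mean minus u × s × (mean dose of those who stopped). That last mean is unknown, so no figure can be put on the difference between arms. If they were treated as missing, the imputation model would be fitted to doses from patients who continued, with no observed post-discharge dose from anyone who stopped to check it against.

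*Effect on any use, only if item 3 alone defined a user.* Recorded share = u × (1 − s). The relative risk (RR), ESP over PAI, is the measure section 2.6.2 names for dichotomous outcomes.

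| True use, ESP / PAI | Stopped, ESP / PAI | Recorded use, ESP / PAI | True RR | Recorded RR |
|---|---|---|---|---|
| 80% / 80% | 30% / 30% | 56% / 56% | 1.00 | 1.00 |
| 80% / 80% | 30% / 10% | 56% / 72% | 1.00 | 0.78 |
| 80% / 80% | 10% / 30% | 72% / 56% | 1.00 | 1.29 |
| 60% / 80% | 30% / 30% | 42% / 56% | 0.75 | 0.75 |
| 60% / 80% | 30% / 10% | 42% / 72% | 0.75 | 0.58 |
| 60% / 80% | 10% / 30% | 54% / 56% | 0.75 | 0.96 |

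For example, 0.80 × 0.70 = 0.56, 0.80 × 0.90 = 0.72, and 0.56 / 0.72 = 0.78. With equal stopping the factor (1 − s) cancels and the RR is unbiased. Precision still falls: power of the chi-squared test at 30 per arm is about 39% for 60% against 80%, and about 20% for 42% against 56%.

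**The case against.** A reader might infer that a patient who stopped is scored as a non-user with zero dose. The article does not say so. It has no zero-dose rule and no definition of a non-user, multiple imputation is the stated method for missing outcomes, and Table 2 is not visible. That reading does not stand. Nor does the idea that a stopper's record contradicts itself: having had a first dose and no longer continuing are compatible answers.

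Item 2 limits the harm. It is asked regardless of item 3 and shows that opioid was used. This stands, with one reservation: item 2 does not say whether doses given in hospital count, so a first-dose time alone may not prove use at home.

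The objective can be read as status at 24 hours rather than consumption over the first day. That is a fair reading of section 1.2, but the follow-up in item 3 asks for an amount over a window, so the call does set out to measure a quantity taken. A trained assistant might also probe beyond the printed words, or a patient might answer yes on hearing the 24-hour window. Either may happen, but the article does not secure it.

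Finally, the percentages above describe the share of users, while what is certainly lost is the amount. That is correct. They show how the mechanism could act if item 3 alone defined use; they do not estimate a bias in this trial. Differences in timing and site of injection do not by themselves show that stopping would be unequal.

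**Conclusion.** The point holds as a limited defect in data capture. Followed as printed, the 24-hour call does not collect the post-discharge opioid amount for a patient who used opioid and stopped before the call, and the article does not say how such a patient's no is scored. Either obvious handling is weak: zero understates the dose, and imputation borrows from patients who continued.

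The size cannot be fixed from the documents. On assumed use of 80% and stopping of 10% to 30%, 2.4 to 7.2 of 30 patients per arm would lack an amount. Equal stopping leaves the relative risk of use unchanged. Stopping of 30% in one arm and 10% in the other would turn a true relative risk of 1.00 into 0.78 or 1.29, but only if item 2 were ignored when defining use. The documents do not support a claim that the comparison will be biased in a particular direction.

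Severity is minor: one secondary outcome by telephone. The primary outcome and the sample size are not affected.

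**What to change.** In the 24-hour script, replace the opening of item 3 with a question put to every patient: has any opioid been taken since leaving hospital, whether or not it is still being taken; if so, which drug, how many doses and what amount. Derive the post-discharge amount from that answer, and record zero only for patients who took none. Keep whether the patient is still taking opioid as a separate status item. Leave the 1-month wording unchanged.

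The cost is one reworded question, the matching change to the paper form and its REDCap entry, and a slightly longer call. No visit or staff is added.
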